### Interim analyses {21b}

N/A. No interim analysis will be conducted because the adverse effects of participating in this study are minimal for the participants.

### Methods for additional analyses (e.g. subgroup analyses) {20b}

N/A. There are no additional analyses planned.

### Methods in analysis to handle protocol non-adherence and any statistical methods to handle missing data {20c}

Based on the intention-to-treat principle, adolescents will be analysed according to their assigned treatment and excluded from the analyses if they withdraw their consent after being randomized. There will be no replacement of adolescents after withdrawal. To examine the possible influence of missing data, we will repeat the analyses described using datasets in which missing data are imputed with state-of-the-art data imputation methods [66].

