### Additional consent provisions for collection and use of participant data and biological specimens {26b}

Adolescents will be informed that they may withdraw their consent at any moment, while highlighting that data collected up to the point of withdrawal will be used for the study. In addition, they will be asked to give permission to access their data for the purpose of monitoring, by other people from the research team and regulatory authorities that are mentioned in the information letter. Adolescents are also asked if their coded data may be used in follow-up research and if they may be contacted for future research related to this study. Through the consent form, they (and both parents if the adolescent is under [16]) provide their consent for these conditions. This study does not involve the collection of biological specimens.

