##### Criteria for discontinuing or modifying allocated interventions {11b}

Adolescents can withdraw from the study at any time for any reason if they wish to do so without any consequences for their treatment, i.e. they can complete their current assigned treatment (either MBT-early or CBT), but will not be contacted for further assessments. Previously collected data will be included in the analyses.

The research team will register and follow up all potential serious adverse events (SAEs) that might be associated with the treatment (e.g. suicide), which may ultimately lead to the ending of the study. These SAEs will also be reported and discussed at a trial steering committee (TSC). The TSC may decide to end the study prematurely if a significant difference in SAEs (> 5) is shown between the two treatment conditions. For more details on the SAEs, see ‘Adverse event reporting and harms {22}’ section.

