##### Provisions for post-trial care {30}

Throughout the treatment, the mental health professional will, in collaboration with the adolescent, evaluate whether the allocated treatment is sufficiently beneficial or if an alternative treatment might be more appropriate, either within the same mental healthcare institution or elsewhere. After dropping out or completing the allocated treatment, participants can also receive the non-assigned treatment (e.g. receiving MBT-early after completing CBT or vice versa). Based on the intention-to-treat principle, adolescents dropping out of the allocated treatment will be followed for research purposes, unless they withdraw their consent to participate in the follow-up assessments.

The sponsor has a liability insurance which is in accordance with Article 7 of the WMO (Medical Research Involving Human Subjects Act; in Dutch: Wet Medisch-wetenschappelijk Onderzoek met Mensen [WMO]). The risks of participating in this study are minimal. The interviews and assessments may be somewhat burdensome but do not carry specific risks. For this reason, the sponsor is dispensed from the obligation to provide insurance for participating in medical research by the Medical Research Ethics Committee (in Dutch: medisch-ethische toetsingscommissie [METC]) of the Erasmus Medical Center (MC).

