### Sample size {14}

The sample size is determined by the predicted difference between the groups on the primary outcome, the BPDSI-IV-ado [46]. Consistent with previous studies on MBT for adolescents [43, 64] and MBT for adolescents compared with treatment as usual [27], we expect a medium effect size (Cohen’s *d* = 0.50) difference between MBT-early and CBT. Based on the BPDSI-IV-ado and with a two-sided *α* = 0.05, a power of 0.80 and a correlation of 0.50 between the repeated measures, based on Bales et al. [65] and Hutsebaut et al. [43], we require 59 participants in each treatment group (118 in total) with at least 1 follow-up measurement. Because of the vulnerable and unpredictable target population, we anticipate a 10% attrition rate and therefore intend to recruit at least 66 participants per group.

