## Statistical methods

### Statistical methods for primary and secondary outcomes {20a}

Data analysis will be conducted using SPSS Statistics. Treatment outcomes of the primary outcome, severity of BPD symptoms, over time will be examined using multilevel modelling. Multilevel modelling is able to model data from different time points, correcting for the dependency of observations by adding a within-subject correlation structure to the regression model. Another advantage of multilevel modelling is that it is able to handle missing data, by using the available data irrespective of the number of repeated measurements. In other words, adolescents with an incomplete number of follow-up measurements are also included in the treatment outcome analyses.

The interventions will be compared with the intention-to-treat adolescent sample, that is, with all adolescents randomized to either MBT-early or CBT.

A deviance test using restricted maximum likelihood will be used to assess whether random or fixed slopes should be assumed in models for each outcome variable. Subsequently, time will be included as appropriate (i.e. linear, logarithmic) and included in the model together with the treatment group and time by group interactions if likelihood ratio tests show significant improvement. The primary effect size of the treatments will be estimated from baseline to end of treatment and secondary effect sizes from baseline to 12-, 18-, and 24-month follow-up. Additional treatment offered in the follow-up period will be included as a covariate in the estimation of the multilevel models and effect sizes from baseline to 12-, 18-, and 24-month follow-up, as well as a predictor of treatment outcomes at 12-, 18-, and 24-month follow-up.

The secondary outcomes will be analysed similarly using multilevel modelling, in which the type of model is adapted to the outcome if needed (i.e. binary in case of the C-SSRS) from baseline to end of treatment, 12-, 18-, and 24-month follow-up. As noted, additional treatment offered in the follow-up period will be included as a covariate in the estimation of the multilevel models and effect sizes from baseline to 12-, 18-, and 24-month follow-up, as well as a predictor of treatment outcomes at 12-, 18-, and 24-month follow-up.

To examine the possible influence of missing data, we will repeat the analyses described using datasets in which missing data are imputed with state-of-the-art data imputation methods [66].

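### The rule that drops randomised adolescents who withdraw consent contradicts the protocol's own intention-to-treat definition and its promise to use data collected before withdrawal

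*Protocol article*

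**What the plan says.** Four sections of the protocol article govern what happens to a randomised adolescent who withdraws.

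- Section {20c}, on non-adherence and missing data, invokes intention to treat and then says that "adolescents will be analysed according to their assigned treatment and excluded from the analyses if they withdraw their consent after being randomized". It adds: "There will be no replacement of adolescents after withdrawal".
- Section {26b}, on consent provisions, says adolescents may withdraw consent at any time but are told that "data collected up to the point of withdrawal will be used for the study".
- Section {11b}, on discontinuation, covers withdrawal from the study: "Previously collected data will be included in the analyses".
- Section {20a}, on statistical methods, makes the comparison in the intention-to-treat sample, "with all adolescents randomized to either MBT-early or CBT". It describes as an advantage of the multilevel model that "adolescents with an incomplete number of follow-up measurements are also included in the treatment outcome analyses".

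Section {30} treats leaving treatment as a separate event: "adolescents dropping out of the allocated treatment will be followed for research purposes, unless they withdraw their consent to participate in the follow-up assessments".

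**The concern.** The sections give opposite instructions for the same people. An analyst working from {20c} and one working from {20a}, {26b} and {11b} would build different primary analysis sets, both calling the result intention to treat. If this is not settled beforehand, the choice could be made after results are known.

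The {20c} rule is also the weaker of the two. It selects on an event that occurs after randomisation. Section {17a} leaves adolescents, parents and therapists unblinded, so the decision to withdraw could depend on the arm and on how treatment is going. Excluding such adolescents gives up the protection of randomisation for that part of the sample. It also departs from what participants are told will be done with their data.

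**Working it through.** **1. Is it the same event?** Sections {20c} and {26b} have the same trigger, withdrawal of consent. Section {20c} removes the adolescent; {26b} uses the data collected so far. Distinguishing treatment dropout from consent withdrawal, as {30} does, therefore does not reconcile them. Section {11b} sides with {26b}, and {20a} sets the population as everyone randomised. Section {20c} is the outlier.

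**2. Could {20c} mean only data after withdrawal?** The text excludes adolescents, not later observations. Sections {11b} and {18b} say that those who withdraw are not contacted for further assessments, so no later data would exist. On that reading the clause would have no effect.

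**3. What would be lost?** Sections {26a} and {16c} place the baseline assessment before randomisation, so every randomised withdrawer should have a baseline record. The primary outcome is the change in BPDSI-IV-ado from baseline to end of treatment, while follow-up runs to 24 months. An adolescent who completes the end-of-treatment interview and withdraws consent later has a full primary endpoint, which {20c} would delete. The imputation analysis cannot be relied on to restore these adolescents, since it repeats the analyses already described.

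**4. The plan's own figure for loss.** Sample size {14} needs 59 per group with at least one follow-up measurement and allows 10% attrition: 59 / (1 − 0.10) = 65.6, rounded up to 66 per group, 132 in total. This reproduces. Ten per cent of 132 is 13.2 adolescents. The figure is overall attrition; no rate of consent withdrawal is given, overall or by arm.

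**5. Illustrative size.** If a proportion p1 of one arm and p0 of the other is excluded, and withdrawers score δ SD worse than those who stay, the arm difference shifts by about (p1 − p0) × δ relative to analysing everyone's observed scores. All rates here are assumptions.

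| p1, p0 | δ = 0.5 | δ = 1.0 |
|---|---|---|
| 15%, 5% | 0.10 × 0.5 = 0.05 SD | 0.10 × 1.0 = 0.10 SD |
| 6%, 4% | 0.02 × 0.5 = 0.01 SD | 0.02 × 1.0 = 0.02 SD |
| 10%, 10% | 0 | 0 |

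Against the design effect of d = 0.50, the top row is 0.05 / 0.50 = 10% to 0.10 / 0.50 = 20%. Its direction is unknown, because the documents do not say which arm would lose more.

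**6. How much the fix could recover.** The shift is recoverable only through withdrawers who already have an end-of-treatment score. If a fraction f of withdrawers has one, equal in both arms, the directly recoverable part is f × (p1 − p0) × δ. For the 15% and 5% scenario this is 0.05 to 0.10 SD at f = 1, 0.025 to 0.05 SD at f = 0.5, and nothing at f = 0. For those with a baseline only, the model has no later score to use. If their baselines resemble those of others, the retained record says nothing about their worse later course.

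**The case against.** The best defence is that {20c} is loosely worded, that three other sections already favour retention, and that the effect on the estimate is probably small. The first part does not hold, because the clause read narrowly would do nothing. The point about size largely stands, and it limits what may be claimed.

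- A reader might infer a known bias of 10% to 20% of the target effect. The documents do not support that. The 15% and 5% scenario averages to 10%, so it assigns the whole attrition allowance to consent withdrawal. That allowance is set against having at least one follow-up measurement, and the protocol also recognises treatment dropout with continued follow-up ({30}) and refusal of a single assessment ({18b}). The scenario further needs every withdrawer to have an end-of-treatment score.
- A reader might infer that the rule defeats the purpose of the multilevel model. It does not. Adolescents who miss assessments or leave treatment stay in the model; only consent withdrawers are removed.
- A reader might infer that the whole trial is open. The research assistants who administer the primary interview are kept blind ({17a}). The concern is arm-dependent withdrawal, which is possible but not documented, rather than biased rating.
- A reader might want a rule for erasing data on request. None of these sections provides one, and resolving this contradiction does not require it.

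**Conclusion.** The contradiction is explicit and concerns who is in the primary analysis. As written, {20c} is a post-randomisation exclusion under an intention-to-treat label, and it conflicts with {26b}, {11b} and {20a}. It would discard baseline data and, for late withdrawers, an observed primary endpoint. It should be corrected before the analysis.

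The conclusion rests on the text and not on a bias estimate. The size of any bias cannot be computed from the documents. The 0.05 to 0.10 SD figure is an upper bound for one assumed scenario, and the part the fix would recover depends on how many withdrawers have already completed the end-of-treatment interview, which is not given.

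**What to change.** Delete the exclusion clause in {20c}. State in its place that all randomised adolescents are analysed in their allocated arm, using all data collected up to withdrawal, in line with {26b}, {11b} and {20a}. Report the number of consent withdrawals by arm.

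The cost is one sentence in the protocol, carried into any analysis plan, and one line in the participant flow. No new data are needed, and the consent information described in {26b} already provides for this use.

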In response to the need for appropriate and in-time treatments, and the lack of evidence of treatment programmes for young people with BPD, the past decades have witnessed the development and evaluation of a range of treatment programmes for young people with BPD features, based on adaptations of treatments for BPD in adults. These include dialectical behaviour therapy (DBT-A) [19], mentalization-based treatment (MBT-A) [20], and transference-focused psychotherapy [21]. The evidence base for these adaptations is rather scarce. A recent review identified only ten randomized clinical trials [22–31]. The results indicate that the majority of these trials did not show the superiority of the specialized treatments compared with treatment as usual. Dropout rates varied widely, ranging from 15 to 75%. Moreover, the heterogeneity of the samples involved in these studies is typically large [17, 22]. Compared with treatments for adults with BPD, the majority of psychosocial treatments for young people with BPD were relatively brief (e.g. HYPE, consisting of sixteen sessions [23]) or were characterized by low treatment intensity (e.g. DBT-A, involving weekly sessions [26]). This matches a clinical staging perspective, with increasing consensus that such interventions, whether brief or low-intensity, may be best suited for addressing the early stages of BPD, characterized by low to moderate risk profiles [32]. However, these interventions are likely to be insufficient for young people with BPD at a later stage of development. A clinical staging approach may enable better matching of treatment to the clinical needs of these young people [10, 33]. Staged care has been introduced as an alternative to stepped care [34]. The advantages of such an approach are clear. Staged care does not require individuals to fail prior treatment to be assigned to more specialist services and it enables to match the type and level of care to the clinical needs associated with the stage of illness, also minimizing the probably of early dropout and dissatisfaction with and disbelief in mental health treatments.

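### The only stated check on missing outcomes repeats the same analyses on imputed data without naming a missingness assumption; if that assumption is missing at random, the check cannot reveal informative loss

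*Protocol article*

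**What the plan says.** All references are to the protocol article.

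- **Main analysis ({20a}).** A multilevel model is fitted to the intention-to-treat sample of everyone randomized. On missing data, the article says of this model that "it is able to handle missing data, by using the available data irrespective of the number of repeated measurements".
- **Check ({20a} and {20c}).** The same sentence appears in both sections: "To examine the possible influence of missing data, we will repeat the analyses described using datasets in which missing data are imputed". The imputation is described only as up to date, with one cited source. No missingness mechanism, imputation model or departure from the main assumption is named.
- **Withdrawal.** Under {20c}, adolescents are "excluded from the analyses if they withdraw their consent after being randomized". Under {11b}, those who withdraw may finish treatment "but will not be contacted for further assessments", and "Previously collected data will be included in the analyses". The consent provisions ({26b}) also say that data collected before withdrawal will be used.
- **Stopping treatment.** Under {30}, adolescents who drop out of treatment stay in follow-up unless they withdraw consent to it. Under {18b}, those who refuse one assessment are invited to the next.
- **Assessment times (Table 1).** The BPDSI-IV-ado is taken at baseline, end of treatment and 24 months. The PHQ-9, GAD-7, BSI, LPFS-BF 2.0 and the parent-completed CBCL are taken at all five times.
- **Expected loss ({14}).** Attrition is put at 10%, with 66 recruited per group to keep 59. On earlier trials, the background ({6a}) says "Dropout rates varied widely, ranging from 15 to 75" per cent. It also puts premature treatment dropout among young people with BPD at about 40–50%.

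**The concern.** The check has a stated purpose, to examine the influence of missing data, so it is fair to ask whether it can serve that purpose. A likelihood-based multilevel model on available data is valid when outcomes are missing at random given what is in the model. Imputation in its ordinary form makes much the same assumption. Two analyses that share an assumption tend to agree whether or not it is true.

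The article gives some reason to doubt the assumption. Its background section suggests that dropout reflects treatment poorly matched to these patients, and says that failed treatment leads to distrust of services. Adolescents who leave the study are not approached again. On the BPDSI-IV-ado itself, someone lost before end of treatment has only a baseline value. If loss is related to unobserved outcome, and differs between arms in amount or in kind, the primary effect shifts. A missing-at-random repeat would reproduce the shifted estimate and could be read as reassurance.

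**Working it through.** **1. The plan's own figure.** Inflating for attrition gives 59 / (1 − 0.10) = 65.6, rounded up to 66 per group, as stated. The 59 was not reproduced: with d = 0.50, two-sided 0.05, power 0.80 and correlation 0.50, a change-score comparison needs 63 per group and a baseline-adjusted one 48. The article does not give its formula, 59 lies between these two values, and nothing below depends on it.

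**2. Shift in the effect.** Let p be the share of missing end-of-treatment scores in an arm. Let s be how much worse, in SD, those participants are than missing-at-random prediction implies. The benefit of MBT-early is overstated by

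p(MBT) × s(MBT) − p(CBT) × s(CBT).

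Only the 10% and the d = 0.50 come from the article ({14}). The other missing shares and every s are assumptions.

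| Missing MBT / CBT | s MBT / CBT | Calculation | Overstatement | Relative to d = 0.50 |
|---|---|---|---|---|
| 10% / 10% | 0.5 / 0 | 0.10 × 0.5 − 0 | 0.05 SD | 10% |
| 20% / 20% | 0.5 / 0 | 0.20 × 0.5 − 0 | 0.10 SD | 20% |
| 10% / 30% | 0.5 / 0.5 | 0.05 − 0.15 | −0.10 SD | −20% |
| 10% / 10% | 0.5 / 0.5 | 0.05 − 0.05 | 0 | 0 |

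The third row goes against MBT-early, so it is conservative for the superiority claim.

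**3. Would a missing-at-random repeat show it?** This was simulated with 66 per arm, correlation 0.5, no true difference, equal missing shares in both arms, and MBT-early dropouts worse by delta. There were 1,500 replicates and 20 imputations each. A baseline-adjusted available-case regression stood in for the multilevel model. Imputation used arm and baseline only. Negative values favour MBT-early.

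| Missing | Delta (SD) | Available-case estimate | Imputed estimate | Correlation of the two |
|---|---|---|---|---|
| 10% | 0.5 | −0.053 | −0.053 | 0.9975 |
| 10% | 1.0 | −0.100 | −0.100 | 0.9973 |
| 20% | 0.5 | −0.105 | −0.105 | 0.9946 |
| 40% | 0.5 | −0.198 | −0.198 | 0.9891 |

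With complete data the mean estimate was within 0.005 of zero in every row. The two methods carry the same bias and are nearly interchangeable.

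**4. Delta at which significance is lost.** Assume an observed d of 0.50 and a shortfall in MBT-early only. Then

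SE = √(2v / [66(1 − p)]) and tipping delta = (0.50 − 1.96 × SE) / p,

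with v = 1 for a change score (2 × (1 − 0.5)) and v = 0.75 with baseline adjustment (1 − 0.5²).

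- p = 10%: SE 0.183 or 0.159, giving a delta of 1.40 or 1.89 SD.
- p = 20%: SE 0.195 or 0.169, giving 0.59 or 0.85 SD.
- p = 40%: SE 0.225 or 0.195, giving 0.15 or 0.30 SD.

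At the planned attrition, only a very large shortfall would overturn a result of the size planned for.

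**The case against.** - **The missing-at-random assumption is inferred.** A reader might take it as settled that the imputation assumes this. The article does not say so, the cited source is not at hand, and imputation can also be done under other assumptions. This stands, so the point is conditional. What remains is that the stated check names no assumption, and its ordinary reading gives it little power to do its job.
- **Detail belongs in the analysis plan.** The imputation model and delta values commonly sit in a statistical analysis plan, which may exist and is not shown. This also stands: their absence from a condensed article is no fault. The point concerns the check that the article does state, and whether it suits its declared purpose.
- **The cited dropout rates are not missing-outcome rates.** A reader might infer 40–50% or 15–75% missing primary outcomes. The documents do not support that. The 40–50% is dropout from treatment, the 15–75% is not described as loss to assessment, and this trial keeps treatment dropouts in follow-up and re-invites those who miss a visit. The rates suggest that loss may be informative, not how large it will be.
- **Withdrawals are not covered by the imputation.** A reader might suppose that the repeat handles adolescents who withdraw. As {20c} is worded they are left out, so neither the repeat nor a delta adjustment would reach them. That conflicts with {11b}, {26b} and the all-randomized analysis set in {20a}.
- **Auxiliary scores could help.** The questionnaires collected at every time could inform the imputation and make the repeat somewhat more informative than the simulation, which used none. This is a fair limit on step 3, but the article does not say that they will be used.

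**Conclusion.** The point holds as a modest, inexpensive improvement to the sensitivity analysis. The one stated check names no missingness assumption. If it is the usual missing-at-random imputation, it largely shares the main model's assumption and cannot show whether informative loss affects the primary result.

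For a 0.5 SD shortfall in one arm, the effect moves by about 0.05 SD at the planned 10% attrition and about 0.10 SD at an assumed 20%. The shortfall and any missing share above 10% are assumptions.

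A reader might go further and conclude that the main analysis is wrong or the primary effect biased. The documents do not support that: available-data multilevel modelling is a reasonable primary analysis, planned attrition is low, and unequal loss could as easily work against MBT-early as for it.

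**What to change.** 1. State the missingness assumption of the planned imputation.
2. Keep the imputed repeat, with PHQ-9, GAD-7, BSI, LPFS-BF 2.0, CBCL and treatment dropout as auxiliary variables.
3. Add a delta-adjusted version. Worsen imputed end-of-treatment BPDSI-IV-ado scores by 0, 0.25, 0.5 and 0.75 SD, once in both arms and once in MBT-early alone. Extend the range until the conclusion changes, and report that delta. The extension matters because at 10% missing the tipping point could lie near 1.4 to 1.9 SD, beyond the starting grid.
4. Reconcile {20c}, which excludes those who withdraw consent, with {11b} and {26b}, which use data up to withdrawal, and with {20a}, which analyses everyone randomized. Unless these adolescents stay in the analysis set, the check cannot reach them.

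The cost is about one paragraph in the analysis plan and a few extra runs on datasets that are to be imputed anyway, using scores already collected. The downside is one more sensitivity table, which may show a less robust result.
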